### Outcome

#### Primary outcomes

Number of screen-positive high-risk women taking 75 mg aspirin developing preterm PENumber of screen-positive high-risk women taking 150 mg aspirin developing preterm PE

#### Secondary outcomes

*Fetal*
AbortionPreterm birthBirth weightStillbirthNICU admissionApgar score <7Early neonatal deathIntracranial bleeding
*Maternal*

**Intrapartum**
Bleeding—GI bleedGestational HTEclampsiaHELLPAbruptionAcute kidney injuryMode of delivery
*Postpartum*
Post partum hemorrhageHDU/ICU stayHematoma formationMortality

### Sample size

The sample size calculation is based on a study by Kumar (2020), according to which the expected proportion of PE in the two groups receiving 75 mg versus 150 mg aspirin was 17% and 6.5% respectively [10].

The sample size has been calculated according to the formula given by Sahai and Kurshid (1996):^74^
$$\text{Sample size}\;N=\frac{\left\{z_{\left(1-\alpha/2\right)}\sqrt{2 \ast \overline p\left(1-\overline p\right)}+z_{\left(1-\beta\right)}\sqrt{p_1\left(1-p_1\right)+p_2\left(1-p_2\right)}\right\}^2}{\left({\text{p}}_1-{\text{p}}_2\right)^2}\;where\;\widehat p=\frac{p_1+p_2}2$$

Expected proportion in the first group: *p*₁ = 0.17 (17%).

Expected proportion in the second group: *p*₂ = 0.065 (6.5%).

*p̂*: (*p*₁ + *p*₂)/2 = 0.1175.

Type I error: *α* = 0.05 (5%), $${z}_{\left(1-\alpha /2\right)}$$ = 1.96, CI = 95%

Type II error: *β* = 0.20 (10%), $${z}_{\left(1-\beta \right)}$$ = 0.842, power = 80%

Based on the formula and values given above, the sample size calculated per group is 146.6 ≈ 147 (total 294).

Allowing for 20% attrition, we get a sample size of 294/0.8 ≈370 (185/group).

Thus, with 80% power and 95% confidence interval, the minimum sample size required for the study is *185* in each group (total 370).

Reference for the formula:

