**Methods:**

This prospective randomized double-blind clinical trial aims to compare the efficacy and safety of 75 mg versus 150 mg aspirin for preventing preterm pre-eclampsia in high-risk women. Screen-positive women aged 18–45 years with singleton pregnancies between 12 and 16 weeks of gestational age will be enrolled. They will be randomized in a 1:1 ratio to receive either 75 mg or 150 mg of aspirin nightly until 37 weeks of pregnancy or earlier if preterm pre-eclampsia develops. Feto-maternal outcomes, including preterm pre-eclampsia incidence and neonatal and maternal complications, will be assessed. The sample size calculation based on expected proportions of preterm pre-eclampsia in both groups indicates a total of 370 participants (185 per group) accounting for 20% attrition.

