### Recent studies and trials

A recent study conducted in China compared the effects of a placebo versus 75 mg daily LDA on pre-eclampsia incidence. The results indicated that 10.43% of women in the LDA group and 22.52% in the control group developed pre-eclampsia. The odds ratio for developing pre-eclampsia with LDA was 0.40 (95% CI = 0.20–0.82, *P*= 0.0098), suggesting a significant benefit of aspirin prophylaxis [21].

Wright and colleagues found that aspirin reduced the length of stay in neonatal intensive care units by approximately 70%, primarily due to a decrease in the rate of iatrogenic prematurity at < 32 weeks gestation, related to early prevention of pre-eclampsia. This reduction in NICU stay was associated with implications for both short-term and long-term healthcare costs and infant survival [22].

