### Effectiveness in specific populations

A multicenter, double-blind, randomized placebo-controlled trial assessed 1776 women at high risk for preterm pre-eclampsia. Participants received either 150 mg daily aspirin or placebo from 11 to 14 weeks of gestation until 36 weeks. Preterm pre-eclampsia rates were 1.6% in the aspirin group and 4.3% in the placebo group. The study concluded that low-dose aspirin effectively prevents preterm pre-eclampsia [23].

Rolnik and colleagues conducted the ASPRE trial, involving 26,941 singleton pregnancies, to screen for preterm pre-eclampsia using a combined algorithm of maternal factors and biomarkers. Women with a preterm pre-eclampsia risk > 1 in 100 were assigned to receive 150 mg daily aspirin or placebo from 11–14 weeks until 36 weeks. The study showed a 62% reduction in preterm pre-eclampsia incidence with aspirin [23].

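### The 80% power is unsupported for the primary endpoint: the design rates of 17% and 6.5% are labelled PE in one place and preterm PE in another, and neither label supports it

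*Protocol article*

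**What the plan says.** All references are to the protocol article.

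- **Sample size:** "the expected proportion of PE in the two groups receiving 75 mg versus 150 mg aspirin was 17% and 6.5% respectively". Two-sided α is 0.05 (z = 1.96) and z for power is 0.842. The result is 147 per group, raised to 185 for 20% attrition. The section concludes that "with 80% power and 95% confidence interval, the minimum sample size required for the study is" 185 in each group. It prints β as 0.20 with 10% in brackets.
- **Abstract, Methods:** "The sample size calculation based on expected proportions of preterm pre-eclampsia in both groups indicates a total of 370 participants". This is the same calculation, with the inputs now called preterm.
- **Primary outcomes:** the count of "high-risk women taking 75 mg aspirin developing preterm" PE, and the same count on 150 mg. The Comparison section records onset before 37 weeks.
- **Effectiveness in specific populations:** in a trial of 150 mg against placebo, "Preterm pre-eclampsia rates were 1.6% in the aspirin group and 4.3% in the placebo group". That section describes selection at a risk above 1 in 100. The Population section here enrols at 1:100 and greater.
- **Statistical analysis:** chi-squared test for categorical data, with Fisher's exact test when more than 25% of cells have an expected count below 5.

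**The concern.** Preterm PE is a subset of PE, and the article keeps the two apart; its Introduction, for example, gives separate detection rates for preterm and term disease. A power statement belongs to one endpoint and one pair of rates. Here the pair carries two labels, and the 80% is presented as the power of the trial without saying which endpoint it covers.

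The trial is a superiority comparison of two doses, intended to inform dosing guidance. If preterm PE is much rarer than 17% and 6.5%, few primary events will occur and the chance of detecting a real difference between the doses will be well below the stated figure. Readers of the result would then be relying on a power that was never calculated for the endpoint tested.

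**Working it through.** **1. The stated figure.** Inputs from Sample size: p₁ = 0.17, p₂ = 0.065, mean 0.1175, z = 1.96 and 0.842.

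n = [1.96·√(2 × 0.1175 × 0.8825) + 0.842·√(0.17 × 0.83 + 0.065 × 0.935)]² / 0.105²
= (0.8926 + 0.3783)² / 0.011025 = 1.6152 / 0.011025 = 146.5, so 147 per group.

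Attrition: 294 / 0.8 = 367.5, rounded in the article to 370. The arithmetic is sound; the question is what the inputs measure.

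**2. Method for power.** Two figures are used, at 147 (evaluable) and 185 (no attrition) per arm.
- *Test rule:* both binomial distributions are enumerated and the test in Statistical analysis is applied. With equal arms, the two event cells (half of the four cells) each have an expected count of half the total events, so Fisher's test applies when there are fewer than 10 events in all.
- *Printed formula:* the Sample size formula solved for power, Φ{[|p₁ − p₂|√n − 1.96√(2p̄(1 − p̄))] / √(p₁(1 − p₁) + p₂(1 − p₂))}.

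At 17% against 6.5% these give 82%/90% (test rule) and 80%/88% (formula).

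**3. If 17% and 6.5% are any-PE rates.** The article gives no preterm share, so one must be assumed. The risk ratio is kept the same.

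| Assumed preterm share | Rates, 75 mg vs 150 mg | Test rule, 147 / 185 | Formula, 147 / 185 |
|---|---|---|---|
| 80% | 13.6% vs 5.2% | 71% / 81% | 70% / 79% |
| 50% | 8.5% vs 3.25% | 48% / 58% | 48% / 57% |
| 25% | 4.25% vs 1.625% | 19% / 28% | 26% / 32% |

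**4. If they are preterm-PE rates.** Against the cited preterm-PE rates, 17 / 4.3 = 4.0 and 6.5 / 1.6 = 4.1, so both are about four times as high. No preterm-PE rate on 75 mg is cited. Taking the placebo 4.3% as a stand-in for 75 mg (an assumption):
- Formula at n = 147: (0.027 × √147 − 0.4690) / 0.2385 = −0.594, so power is 28%.
- Formula at n = 185: (0.027 × √185 − 0.4690) / 0.2385 = −0.427, so power is 33.5%.
- Test rule: 20% and 30%. It is lower because few events are expected, 147 × 0.059 = 8.7 and 185 × 0.059 = 10.9, so Fisher's test often applies.

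**5. Detectable difference.** With 150 mg at 1.6%, 80% power under the test rule needs a 75 mg rate of about 8.5% at 147 per arm (difference 6.9 points) or 7.5% at 185 (5.9 points).

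**The case against.** The strongest reply is that the Sample size section may simply have dropped the word preterm. The abstract would then be right, and the 80% would belong to the correct endpoint. That is possible, and a reader who infers that the plan definitely used any-PE rates goes further than the documents allow. It does not rescue the claim, because the article would then expect 17% preterm PE on an active dose while citing 4.3% on placebo at nearly the same risk cut-off, without explanation.

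A second reply is that the cited rates may not transfer. This is a single tertiary hospital in India, uterine artery Doppler is optional, and South Asian origin is listed as a risk factor. The Comparison section counts onset before 37 weeks, while the description of the first-trimester test speaks of delivery before 37 weeks; counting by onset could give a higher rate. The review summarised in the article gives PE incidence of 4 to 30% in women at increased risk, which contains both design rates. All of this stands as a reason to present power as conditional. But that range is for PE, and no higher preterm-PE rate is cited.

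Two further inferences are tempting and should not be drawn.
- *That power is 20 to 30% at best.* This is not a bound. It rests on a placebo rate standing in for 75 mg, and an assumed preterm share of 50 to 80% of the design rates gives 48 to 71% at 147 per arm.
- *That the plan assumes 75 mg has no effect,* because the assumed reduction between doses (1 − 6.5/17 = 62%) matches the 62% cited for 150 mg against placebo. Equal relative reductions in different populations do not imply that. The 17% is attributed to a comparison of the two doses, not derived from placebo. In the cited study of 75 mg, "10.43% of women in the LDA group and 22.52% in the control group developed pre-eclampsia", and 17% would itself be below that control rate.

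**Conclusion.** Wrong as written. The two labels contradict each other, and the 80% power is unsupported for preterm PE under both.

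Under the test rule at the planned evaluable number of 147 per arm, power for preterm PE is about 71%, 48% or 19% if the rates are any PE and 80%, 50% or 25% of cases are preterm (assumed shares, same risk ratio). At the cited 4.3% and 1.6% it is about 20%, or 28% by the printed formula; with no attrition these become 30% and 33.5%. The placebo stand-in is generous unless 75 mg is worse than placebo, since any benefit of 75 mg narrows the contrast.

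Only the most favourable share combined with no attrition comes near the stated figure (81% by the test rule, 79% by formula). The true power cannot be fixed from the documents. A reader might conclude that a null result is the likeliest outcome; that follows only under the lower-rate assumptions.

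**What to change.** - Check the source study, then make the Sample size section and the abstract agree on which endpoint 17% and 6.5% measure. Neither label should be adopted without that check. The reference number attached to these rates is also used in the Introduction for cardiovascular prevention after PE, so the citation should be verified too.
- Limit the 80% power statement to those rates and that endpoint.
- Add the power for preterm PE at 4.3% and 1.6%, stating that placebo stands in for 75 mg, and give the detectable difference at 147 and 185 per arm.
- Correct the bracketed percentage after β = 0.20 from 10% to 20%, which is what z = 0.842 and 80% power imply.

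A sentence saying that a non-significant result will not be read as equivalence of the doses would help, but it is optional; the article makes no equivalence claim.

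The cost is rewording of two sections and probably a less favourable stated power. No change in enrolment is asked for.

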### Implementation strategy

All women 18–45 years attending ANC and Fetal medicine OPD of VMMC & Safdarjung hospital between 11 and 13 + 6 weeks of gestational age (crown-rump length of 45–84 mm) will be screened for preterm PE using the first-trimester quadruple testing.

#### First-trimester quadruple Test (1 T Quad Test)

First trimester quadruple test includes maternal characteristic along with PAPA, PLGF, Free beta HCG, and alfa fetoprotein (AFP). Pre-eclampsia risk calculation will be done using maternal characteristics that increase the risk of pre-eclampsia, i.e., advanced maternal age, increased weight, Afro-Caribbean and South Asian racial origin, chronic hypertension, diabetes mellitus, systemic lupus erythematosus, antiphospholipid syndrome, in vitro fertilization conception, family history or personal history of pre-eclampsia, and first pregnancy. Using maternal characteristics along with MAP, PIGF, and PAPP-A with/without UTPI risk of preterm PE will be calculated.

Placental growth factor (PlGF) and pregnancy-associated plasma protein-A (PAPP-A) are significantly reduced in the first trimester and throughout the pregnancy in women that will later develop preterm pre-eclampsia with delivery < 37 weeks gestation. Of these two markers, PlGF has higher sensitivity for pre-eclampsia screening than PAPP-A. Biophysical markers such as mean arterial blood pressure (MAP) at 11–13 + 6 weeks’ gestation is higher in women that will later develop pre-eclampsia compared to unaffected pregnancies and is particularly raised in those women who develop the early preterm PE. The MAP will be calculated using two simultaneous recordings taken from both the arms. After the first measurements, wait for 1 min from the moment of cuff deflation and then a repeat set of measurements will be taken again from both arms. So a total of four measurements will be taken and the online calculator will then calculate the MAP multiple of the median (MoM), adjusted for the mother’s weight, height, race, smoking, chronic hypertension, diabetes, family history of pre-eclampsia, and previous history of pre-eclampsia. Only automated blood pressure monitors that are validated for use in pregnancy and pre-eclampsia will be used. The uterine artery pulsatility index (UTPI) will not be mandatory and if performed will be measured by transabdominal/transvaginal ultrasound examination at 11–13 + 6 weeks.

Prediction model for PE < 37 weeks using maternal factors + MAP along with PAPP-A and PIGF has a detection rate (DR) of 73% with 10% FPR. Adding uterine artery PI (UTPI) increases DR to 80% with FPR of 10%. 1 T Quad will be done using Perkin Elmer LifeCycle 7.0 software on Victor 2D Instrument (Time Resolved Fluorescence—DELFIA). PerkinElmer LifeCycle 7.0 software will generate a report in which a woman’s individual risk for developing preterm pre-eclampsia will be clearly presented and color coded (red = increased risk). The day IT Quad will be carried out will be visit 0.

Women with risk for preterm PE 1:100 and greater will be labeled as screen positive or high risk. Prior to any trial-related activity, the investigator will be given the verbal information and written information in a printed form about the trial to the participant/guardian(s) which they can read and understand. The investigator would ensure that the participant is fully informed about the aims, procedures, discomforts, and expected benefits of the trial. It will be emphasized that participation is voluntary and participants have the right to opt out of the trial at any time without any prejudice. A voluntary, signed informed consent will be obtained from the participant prior to clinical trial-related procedure.

#### Study procedure

All screen-positive women fulfilling the criteria will be enrolled at 12–16 weeks of pregnancy after signing the consent form. The required baseline investigations will be carried out and that day will be visit 1 or baseline. Previous obstetric history, pre-pregnancy weight, and past history of preeclampsia will be recorded. Weight and height will be recorded. Blood pressure will be measured on the right arm in a sitting position, and urine albumin/sugar test will be performed. After enrolment, the women will be randomized to receive 75 mg or 150 mg aspirin at night from 12 to 16 weeks of pregnancy. The drug will be dispensed to her after fulfilling all the formalities as per the protocol.

The subsequent follow-up will be at 20 weeks (visit 2), and four-weekly till 28 weeks, i.e., at 24 weeks (visit 3) and at 28 weeks (visit 4). After 28-week period of gestation, participants will be called two-weekly till 36 weeks, i.e., 30 weeks (visit 5), 32 weeks (visit 6), 34 weeks (visit7), and 36 weeks (visit 8). Participant will be called weekly after 36 weeks, i.e., 37 weeks (visit 9). Aspirin will be stopped at 37 weeks or earlier to 37 weeks if onset of preterm preeclampsia. If they do not develop PE, then they will be called weekly at 38 weeks (visit 10), 39 weeks (visit 11), and 40 weeks (visit 12). Subjects will visit the investigating site 12 times during the trial or if participant is not able to visit; a senior research fellow recruited in the project will visit her at her residence..Participants will be followed and whether they have onset of preterm PE < 37 weeks will be recorded. In case the women develop PE, the aspirin will be stopped. All participants developing PE and not developing PE women will be followed till delivery and fetomaternal outcome will be noted.

### Ethical consideration

The study was approved by the Institutional Ethics Committee(IEC) of VMMC-Safdarjung Hospital and registry in the Clinical Trial Registry of India; written consent of each enrolled participant will be obtained prior to the enrolment.

### Consent

Written, informed consent to participate will be obtained from all participants.

### Withdrawal criteria

A participant if failed to adhere more than 80% to the requirements of aspirin intake and withdrew consent prior to the completion of the study.Every subject will be free to withdraw from the trial at any point in time for any reason.

The reason for withdrawal will be recorded in the CRF, dated, and signed. Efforts will be made to ascertain the reason for discontinuation.

#### Procurement of trial drugs

Both the aspirin dosages will be available in granules form in identical capsules. Both trial drugs will be packed only for research purposes by the GMP-certified company.

#### Assessment of drug compliance

The compliance of intake of IP will be monitored by assessing the approximate quantity of medicines consumed by the participants (minimum 80%). For this purpose, the participants will be instructed to return the empty container of the medicine at the time of each follow-up visit. Repeated reminders will be given over the phone or through family members by the project staff for regular intake of the medicine.

#### Treatment period

It will be 21–25 weeks in both groups. Study participant will be recruited at 12–16 weeks. The subsequent follow-up will be at 20 weeks (visit 2) and four-weekly till 28 weeks, i.e., at 24 weeks (visit 3) and at 28 weeks (visit 4). After 28-week period of gestation, the participants will be called biweekly till 36 weeks, i.e., 30 weeks (visit 5), 32 weeks (visit 6), 34 weeks (visit7), and 36 weeks (visit 8). Participants will be called weekly after 36 weeks, i.e., 37 weeks (visit 9), 38 weeks (visit 10), 39 weeks (visit 11), and 40 weeks (visit 12). Onset of preterm PE will be recorded, aspirin will be stopped, and participants will be followed till delivery and fetomaternal outcome will be noted. In participants who do not develop preterm PE, aspirin therapy will be stopped at 37 completed weeks and will be allowed to go till 40 weeks (term) if no obstetrical indication for induction and fetomaternal outcome will be recorded. At every visit, history will be taken and they will be asked for any signs and symptoms of preeclampsia; weight and BP will be measured and urine albumin test will be done Fig. 1.

**Fig. 1 Fig1:**
[figure not shown]
Schedule of enrolment, interventions, and assessments according to SPIRIT figure

### Diagnostic criteria for preeclampsia (ACOG 2020)

#### Blood pressure

Systolic blood pressure of 140 mm Hg or more or diastolic blood pressure of 90 mm Hg or more on two occasions at least 4 h apart after 20 weeks of gestation in a woman with a previously normal blood pressureSystolic blood pressure of 160 mm Hg or more or diastolic blood pressure of 110 mm Hg or more. (Severe hypertension can be confirmed within a short interval (minutes) to facilitate timely antihypertensive therapy).

#### Proteinuria

300 mg or more per 24-h urine collection orProtein/creatinine ratio of 0.3 mg/dL or more orDipstick reading of 2 + (used only if other quantitative methods not available) or in the absence of proteinuria, new-onset hypertension with the new onset of any of the following:Thrombocytopenia: platelet count less than 100,000 10^9^/LRenal insufficiency: serum creatinine concentrations greater than 1.1 mg/dL or a doubling of the serum creatinine concentration in the absence of other renal diseaseImpaired liver function: elevated blood concentration of liver transaminases to twice normal concentrationPulmonary edemaNew-onset headache unresponsive to medication and not accounted for by alternative diagnoses or visual symptoms

#### Preeclampsia with severe features

Systolic blood pressure of 160 mm Hg or more or diastolic blood pressure of 110 mm Hg or more on two occasions at least 4 h apart (unless antihypertensive therapy is initiated before this time)Thrombocytopenia (platelet count less than 100,000 10.^9^/L)Impaired liver function that is not accounted for by alternative diagnoses and as indicated by abnormally elevated blood concentrations of liver enzymes (to more than twice the upper limit normal concentrations) or by severe persistent right upper quadrant or epigastric pain unresponsive to medicationsRenal insufficiency (serum creatinine concentration of more than 1.1 mg/dL or a doubling of the serum creatinine concentration in the absence of other renal disease)Pulmonary edemaNew-onset headache unresponsive to medication and not accounted for by alternative diagnosesVisual disturbances

### Study procedure at follow-up

An automated reagent-strip reading device for dipstick screening for proteinuria in pregnant women will be used. If dipstick screening is positive (1 + or more), protein:creatinine ratio (PCR) will be done to quantify proteinuria in pregnant women using 30 mg/mmol as a threshold for significant proteinuria. If a participant is not able to come to the hospital for follow-up, then she will be visited at home by the research officer to ensure drug compliance and supply of study medication and also general follow-up.

### Laboratory investigations

An 8.5-ml (serum—3.5 ml, citrate—3 ml, and EDTA—2 ml) venous blood sample will be obtained after enrolment in the study. Hemogram (hemoglobin, total leucocyte count, DLC), serum TSH, ABO/Rh, VDRL, HIV, HbsAg**,** oral glucose tolerance test, liver, and kidney function tests, i.e., ALT, AST, ALP, total bilirubin, direct bilirubin, total protein, albumin, serum creatinine, urea, vitamin D levels, ionic calcium, coagulation profile, and urine routine and microscopy (urine r/m) of the enrolled participants will be carried out as baseline at the time of recruitment.

Laboratory test, i.e., CBC, LFT, KFT, S. LDH, coagulation profile, urine routine, and microscopy will be done 4 weekly. OGTT will be done first at recruitment, 24–28 weeks and at 32–34 weeks. Anomaly scan will be done at 18–20 weeks. Ultrasound with biometry and doppler will be done 4 weekly from 28 weeks in participant do not developing PE. In participants developing preterm PE, ultrasound with doppler will be done according to severity of the PE. All investigation will be done by NABH accredited lab.

